**ENROLMENT****:**										
Eligibility screen	X									
Informed consent	X									
**Allocation**		X								
**INTERVENTIONS****:**										
***MSTEP***										
***CONTROL***										
**ASSESSMENTS****:**										
**Covariates**										
Parental protectiveness (ARCS)	X									
Demographics and medical history	X									
**Primary outcomes**										
*Concussive symptoms, (HBI)*	X		X	X	X	X	X	X	X	X
*Health-related quality of life (PedsQL)*	X		X	X	X	X	X	X	X	X
**Secondary outcomes**										
*Depression* *(PHQ9)*	X							X	X	X
*Anxiety* *(GAD7)*	X							X	X	X
*Sleep quality* *(ASWS-10)*	X							X	X	X
**Mediators**										
*MVPA*^*g*^ *(accelerometry)*	X							X	X	
*Fear avoidance (FOPQ)*	X							X	X	X

*ARCS* adult responses to children’s symptoms, *HBI* Health and Behavior Inventory, *PedsQL* Pediatric Quality of Life, *PHQ-9* Patient Health Questionnaire-9, *GAD7* Generalized Anxiety Disorder-7, *ASWS-10* Adolescent Sleep Wake Scale-10, *MVPA* moderate-vigorous physical activity, *FOPQ* Fear of Pain questionnaire

### Sample size {14}

We plan to recruit 200 subjects. Given the RCT design and repeated assessments, we calculate power for our primary outcomes (HBI) and (PedsQL) using two-way repeated analysis of variance (ANOVA) with two factors: study group is the between-subject factor, and time point (baseline, 6 weeks, 3 months, and 6 months) is the within-subject factor. To address our main hypothesis of differences in trajectories, we will test the between-within interaction effect, i.e., the interaction between study group and time. If we were to see similar differences in means between the two study groups on HBI and PedsQL as we did in our pilot STEP RCT [16], our planned sample size of 200 would provide > 99% power to detect a significant group-by-time interaction (i.e., differences in trends over time between the groups) in both HBI and PedsQL. This estimate is based on 4 time points, similar but slightly larger variances as we observed in pilot data, and an ICC = 0.5 for moderate within-subject correlations. We also wanted to ensure we would have sufficient power to assess mediation. For this power calculation, we used the regression model approach for single mediator. Vittinghoff [98] showed that for the linear regression, $$ {y}_i={b}_0+{b}_1{x}_i+{b}_2{m}_i+{\epsilon}_i,{\epsilon}_i\sim N\left(0,{\sigma}_e^2\right), $$ testing the mediation effect is equivalent to testing the null hypothesis *b*_2_ = 0 versus the alternative hypothesis *b*_2_ ≠ 0. The sample size depends on power, type I error rate, regression coefficient *b*_2_, standard deviation of the mediator *σ*_*m*_, standard deviation of the error term in the above regression *σ*_*e*_, and the correlation between the predictor *x* and the mediator *m, ρ*_*xm*_. Using residualized change scores from our pilot data for the outcome (HBI) and mediators (MVPA and FOPQ) [16], we found that if we were to observe similar mediation effects from MVPA levels and FOPQ as in our pilot data, our proposed total sample size of 200 would provide 78% power to assess mediation by MVPA and 95% power to assess mediation by FOPQ.

### Recruitment {15}

Patients will be recruited from both local clinic populations and nationally via contact with colleagues who care for youth with concussion and online advertisements.

## Assignment of interventions: allocation

### Sequence generation {16a}

We will utilize block randomization, stratified by severity of concussive symptoms (HBI ≥ 20) and sex at birth, with computer-generated random number sequences.

### Concealment mechanism {16b}

The randomization table will not be visible to the research staff.

### Implementation {16c}

Allocation will occur via REDCap.

## Assignment of interventions: Blinding

### Who will be blinded {17a}

We will describe the study as a comparison between exercise programs, in order to blind participants as to whether they are in the intervention or control arm. The statistician will be blinded to intervention status by labeling the intervention variable non-specifically in the dataset (i.e., 1 and 2). The PI and research coordinators will not be blinded.

Procedure for unblinding if needed {17b}

Not applicable as this is not a pharmaceutical trial.

## Data collection and management

### Plans for assessment and collection of outcomes {18a}

We will collect two types of data: [1] survey data and [2] physical activity data via accelerometry. Please see Table 1 for time points of data collection.

Survey data will be collected online using REDCap and self-report.

Accelerometry data will be collected using the ActiGraph GT3X Link (see section “Outcomes {12}”).

### Plans to promote participant retention and complete follow-up {18b}

Please see section “Strategies to improve adherence to interventions {11c}” as this section was written to pertain both to adherence and retention.

### Data management {19}

Survey data will be stored online in REDCap. When possible, data fields will be limited to ensure data quality (e.g., utilizing ranges for dates). Accelerometry data will be downloaded from actigraphs and merged with other data using unique identifiers.

### Confidentiality {27}

Survey data will be entered and stored in a HIPAA-compliant online database (REDCap) accessed only by study staff. Data from accelerometry will be stored on a server at the Seattle Children’s Research Institute with strictly controlled physical access both at the perimeter and at building ingress points by professional security staff utilizing video surveillance, state of the art intrusion detection systems, and other electronic means for ensuring confidentiality. After data is collected, information which would identify the subjects will be removed and code numbers used instead with the translation between the code and PHI stored in a separate file. All analyses will be conducted with deidentified data.

### Plans for collection, laboratory evaluation, and storage of biological specimens for genetic or molecular analysis in this trial/future use {33}

These are not applicable as these types of data are not being collected.

## Statistical methods

### Statistical methods for primary and secondary outcomes {20a}

The primary outcome analyses will be assessed using intention-to-treat with the predictor of interest being experimental group regardless of adherence with assigned treatment. We will examine the impact of adherence on treatment effects in secondary analyses. Pre-identified potential confounders such as demographics (age, sex, and body mass index [BMI]), baseline biopsychosocial factors (standardized measures of depression and anxiety [PHQ-9 and GAD-7]), baseline clinical factors (history of prior concussion, severity of symptoms, duration of symptoms at entry into the study, outcome measures at baseline), and parental protective behavior (Adult Responses to Children’s Symptoms, ARCS) will be summarized using descriptive statistics. In addition to stratification factors (age, sex, and severity of symptoms), we make the a priori decision to control for biopsychosocial factors, particularly parental protective behavior, as well as any other unbalanced confounders from the list above as independent predictors in all subsequent regression analyses. We will model and compare trajectories of outcome measures using mixed effects models. We choose mixed effects modeling for its ability to account for variation at different levels, flexibility regarding time trend and unequally spaced time points, and ease with management of missing data.

The first part of the primary analysis will examine differences in HBI and PedsQL (primary outcomes) between study arms post-intervention (6 weeks) and follow-up (6 months) respectively. The main analytic tool will be based on covariate-adjusted regression models. The two primary outcomes can be considered as continuous outcomes thus linear regression models will be applied, in which group assignment will be the predictor of interest and other pre-identified confounders will be adjusted as covariates.

The second part of the primary analysis will examine trajectories of concussion symptoms. Given that concussive symptoms (HBI) will be assessed 9 times, we believe the data will provide sufficient resolution to model time as a continuous variable when examining change in HBI over time. Let *Y*_*ij*_ denote the HBI measured for *i*th subject at time *t*_*j*_, *x*_*i*_ denote the group assignment for *i*th subject, and ***Z***_*i*_ denote the vector of covariates; we will consider the following general model specification: $$ (1)\ {Y}_{ij}=f\left({\boldsymbol{\beta}}_i^{\left({x}_i\right)},{t}_j\right)+\boldsymbol{\gamma} {\boldsymbol{Z}}_i+{\epsilon}_{ij};{\boldsymbol{\beta}}_i^{\left({x}_i\right)}\sim N\left({\boldsymbol{b}}^{\left({x}_i\right)},\boldsymbol{\Sigma} \right);{\epsilon}_{ij}\sim N\left(0,{\sigma}^2\right) $$. Function *f*(***β***, *t*) can take flexible functional forms to capture different shapes of trajectories. For example, *f*(***β***, *t*) = *β*_0_ + *β*_1_*t* represents a linear trend over time; *f*(***β***, *t*) = *β*_0_ + *β*_1_*t* + *β*_2_*t*^2^ represents a quadratic trend over time; or more generally, we can assume a restricted cubic spline for *f*(***β***, *t*) to represent more flexible trajectory shapes. Based on our pilot study and prior studies in the literature, we have observed that concussive symptoms and other health outcomes exhibit faster rates of improvement in the acute phase post-injury (< 3 months), with rates then decreasing and leveling off. For these reasons, a more parsimonious and accurate function for time trend could be exponential decay function in the form *f*(***β***, *t*) = *β*_2_ + (*β*_0_ − *β*_2_) × exp(−*β*_1_*t*),where *t* is time, *β*_0_ is the initial value at *t = 0*, *β*_2_ is the asymptote as *t* goes to infinity, *β*_1_, *constrained to be positive*, is the rate of change or how quickly the process decays from the initial value to the asymptote [99]. Parameters ***b***^(1)^ and ***b***^(2)^ are the group specific shape parameters, and equality of these parameters will be tested using multivariate Wald test to assess the hypothesis that concussive symptoms (HBI) decline more quickly in the MSTEP group compared to control. Note the rate of change *β*_1_ could also be influenced by other biopsychosocial variables. We can address this by considering a more advanced hierarchical model in which: [2] log(*β*_1_(*x*_*i*_, ***Z***_*i*_)) = *α*_0_ + *α*_1_*x*_1_ + ***α***_2_***Z***_*i*_, the logarithmic transformation ensures positivity of the change rate and parameter *α*_1_captures the difference in rate of change between study arms.

Health-related quality of life as measured by PedsQL will be assessed at 4 time points. The smaller number of time points limits options for trajectory shapes; thus constraining us to examine changes over time between groups by modeling time as a discrete predictor: (3) *Y*_*ij*_ = *β*_0*i*_ + *b*_1_*x*_*i*_ + *b*_2*j*_*t*_*j*_ + *b*_3*j*_*x*_*i*_ × *t*_*j*_ + *ϵ*_*ij*_; *β*_0*i*_~*N*(*b*_0_, *τ*^2^); *ϵ*_*ij*_~*N*(0, *σ*^2^).

With this specification, the random intercept *β*_0*i*_ captures within-subject correlation, and coefficients for the group-by-time interactions *b*_3*j*_ estimate the differences in changes over time between groups. Individual coefficients can be tested using Wald test, and overall group-by-time interaction can be tested using likelihood ratio test.

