### Methods in analysis to handle protocol non-adherence and any statistical methods to handle missing data {20c}

Multiple imputation (MI) will be used to adjust model estimates that include incomplete data. Specifically, we will generate multiple imputed datasets with missing values filled in using chained equations (MICE). Baseline characteristics will be imputed using predictive mean matching and missing outcomes will be imputed using joint linear mixed models. Regression models will be fitted to each imputed dataset and the results will be pooled to produce the final estimates for inference.

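### The promised covariate adjustment does not reach the group-by-time contrasts: model (3) omits the covariates, main effects would not move its interaction terms, and the one equation letting covariates act on change is optional and HBI-only

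*Protocol article*

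**What the plan says.** All of the following is in the protocol article, Statistical methods {20a}, unless another section is named.

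- **Commitment.** The stratification factors, biopsychosocial factors (parental protectiveness in particular) and any unbalanced confounder are to enter "as independent predictors in all subsequent regression analyses".
- **First part of the primary analysis, 6 weeks and 6 months.** "The main analytic tool will be based on covariate-adjusted regression models".
- **Model (1), HBI over nine visits.** The text lets Z_i "denote the vector of covariates; we will consider the following general model specification", and the model carries these covariates as an additive term γZ_i that does not depend on time. For the group-specific shape parameters, "equality of these parameters will be tested using multivariate Wald test".
- **Equation [2], HBI, exponential form.** The text grants that the rate of change may depend on biopsychosocial variables, then says: "We can address this by considering a more advanced hierarchical model in which" the log rate is a function of group and Z_i.
- **Model (3), PedsQL over four visits.** The number of visits is described as "constraining us to examine changes over time between groups by modeling time as a discrete predictor". The equation has a random intercept, group, visit and group-by-visit. It has no Z_i.
- **Missing data {20c}.** Missing values are imputed first, then "Regression models will be fitted to each imputed dataset".
- **Sample size {14}.** The main hypothesis is a difference in trajectories, tested by the group-by-time interaction, with N = 200 and ICC = 0.5.

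**The concern.** The commitment to adjust covers every later regression, yet the printed PedsQL model has no place for the covariates. Model (1), printed just before it, does show Z_i, so the omission is visible within the article.

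Putting the covariates in as main effects, which is the natural reading of independent predictors, would not cure this. A group-by-time term compares changes within persons. A covariate that adds the same amount at every visit drops out of every change.

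At stake is whether the pre-specified adjustment protects the trajectory contrast against chance imbalance in factors that drive recovery, and whether it gives that contrast any precision. A contrast that ignores the strata used to randomise also carries a standard error that is somewhat too wide.

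**Working it through.** **Plan's own figure.** The only related figure is power above 99% for the interaction ({14}). The pilot means and variances are not given, so it can be neither reproduced nor refuted. With N = 200, four visits, ICC 0.5 and an assumed two-sided alpha of 0.05, a constant post-baseline difference of 0.4, 0.5 or 0.6 SD gives 84%, 96.5% or 99.6% power. The present point does not dispute that figure.

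**Model (3), algebra.** With every visit present, the estimate of b3j is the arm difference in mean change from baseline to visit j. If γZ_i is added at each visit, the change is (Y_ij + γZ_i) − (Y_i0 + γZ_i) = Y_ij − Y_i0. The term cancels. After imputation every analysed dataset is complete, so the cancellation is exact in each one.

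**Model (3), simulated data** (N = 200; all parameter values illustrative):

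- Group-by-time estimate without Z: −4.012 (SE 1.069). With Z as a main effect: −4.012 (SE 1.069).
- When Z truly affects change, group by last visit: −1.658 without Z, −1.658 with Z as a main effect, −2.142 with Z-by-visit.

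**Model (1), forms linear in the parameters.** When Z truly affects change, the group slope is −0.625 without Z, −0.625 with additive Z and −0.867 with Z-by-time. The quadratic and spline forms behave the same way: additive Z moved the group differences in the time terms by no more than 2e-9.

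**Model (1), exponential form:**

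- Additive Z barely moves the group difference in log rate: 0.397 to 0.394 in one dataset, 0.513 to 0.491 in another.
- It does move the differences in starting level and asymptote, by about 0.5 to 2.4 points and with smaller SEs. The joint Wald statistic therefore changes: 28.4 to 26.2, 39.8 to 42.1, 47.7 to 51.7.
- Equation [2] moves the rate contrast itself: 0.512 to 0.546, 0.495 to 0.409, 0.491 to 0.401 in three datasets.

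**Size for the severity stratum (HBI ≥ 20, {16a}).** Inputs: ICC ρ = 0.5 ({14}), outcome variance set to 1, normal scores. The share of youth above the cut is not stated, so it is assumed.

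1. Variance of a baseline-to-visit change = 2(1 − ρ) = 1.
2. Squared correlation of baseline with change = (1 − ρ)/2 = 0.25.
3. Cutting a normal score in two keeps a fraction φ(z)²/[p(1 − p)] of its squared correlation. This is 2/π = 0.637 at p = 0.5 and 0.342 at p = 0.9.
4. Variance of change explained: 0.25 × 0.637 = 15.9% at p = 0.5; 0.25 × 0.342 = 8.6% at p = 0.9.
5. SE inflation if the stratum is ignored: 1/√(1 − 0.159) = 1.09; 1/√(1 − 0.086) = 1.05.

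**Same stratum, linear slope over nine visits.** Take t = 0 to 6, 13 and 26 weeks. The mean is 60/9 = 6.67 and Sxx = 936 − 400 = 536. Squared correlation of baseline with slope = 6.67² × 0.5/536 = 0.0415. Times 0.637 this is 2.6%, an SE ratio of 1/√(1 − 0.026) = 1.013.

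**The case against.** The strongest case on the other side has five parts.

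- **Equation [2] exists.** It lets covariates act on the HBI rate, so it would be wrong to say that covariates enter only as a constant shift. This stands. But the equation is worded as a possibility, applies to the exponential form and to the rate only, and has no PedsQL counterpart.
- **The joint Wald test covers more than the rate.** A reader might infer that the planned adjustment has no effect on the trajectory analysis at all. The article does not support that for HBI: the test includes the starting level and asymptote, which additive Z adjusts. What stands is narrower. The hypothesis attached to that test is faster decline, and adjusting the level does not adjust the decline.
- **The cancellation is not universal.** Fitted to incomplete data (about 25% missing, dependent on Z), model (3) does move when Z is added: −3.036 to −2.782. This is true, but {20c} plans to fit completed datasets.
- **Randomisation already protects the comparison.** Severity and sex are balanced by design, remaining imbalance is chance, and ignoring strata errs on the conservative side. This stands: there is no systematic bias. The first part of the primary analysis is also properly adjusted.
- **The equation may be schematic, with detail left to an analysis plan.** This has some weight. But the article prints Z_i in one primary model and not in the other, after committing to both, and no reading of the commitment as main effects would change b3j.

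A reader might also convert the gain from all covariates into an equivalent number of extra youth. That needs the covariates to relate to follow-up solely through the observed baseline score. In simulation, a covariate tied to a person's stable level, which is plausible for ARCS, PHQ-9 or GAD-7, removed 0% of the variance of change.

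**Conclusion.** The point holds in a limited form. Model (3) contradicts the commitment to adjust all regressions, and main effects alone would leave its group-by-time coefficients exactly as they were in completed data. In model (1) the additive term adjusts level and asymptote but not the change terms of the linear-in-parameter forms, and hardly the exponential rate. The only remedy printed is optional and covers HBI alone.

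The consequence is modest: chance imbalance left in the contrast, some lost precision, and an inconsistency in the plan. For the severity stratum, ignoring it makes the SE of a baseline-to-visit HBI change about 5–9% too wide if 90% to 50% of youth score above the cut. For a nine-visit linear slope the stratum explains about 3% of the variance at the median split. These figures assume ICC 0.5 with equal correlation between visits and normal scores. They are for HBI; the gain for PedsQL depends on how the stratum relates to PedsQL change, which the article does not give.

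**What to change.** - **Model (3).** Add centred Z_i and Z_i-by-visit terms for the strata actually used (HBI ≥ 20 and sex at birth, per {8} and {16a}; {20a} also lists age) and for the pre-specified covariates. If fewer parameters are wanted, use Z_i by post-versus-baseline terms. Centring keeps the arm contrast at the average covariate value.
- **Model (1).** State that Z_i acting on the change parameters is part of the primary analysis: on the slope, quadratic or spline terms, or on the rate through equation [2] if the exponential form is used. Pre-specify a fallback limited to the strata and ARCS if the nonlinear model does not converge.

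**Cost.** No new data. In model (3), at most 3 degrees of freedom per single-degree-of-freedom covariate, out of about 200 × 3 = 600 within-person degrees of freedom. In model (1) there is some real fitting burden if several covariates act within a nonlinear random-effects model on 200 youth, which is why the fallback should be written down in advance.

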### Trial design {8}

Youth with PPCS will be randomized to 6 weeks of either MSTEP (a virtually delivered subthreshold exercise program) or an active control (stretching). This is a superiority trial, testing whether MSTEP is superior to the active control. Randomization will be allocated 1:1 to MSTEP and control, stratified by severity of concussive symptoms and sex at birth. Data will be collected at baseline, weekly during the intervention and at 6 weeks, 3 months, and 6 months.

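### PedsQL model (3): the free baseline arm difference costs about 25% of the variance at the protocol's own ICC, and the random-intercept-only covariance leaves per-visit tests exposed if correlation falls with time

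*Protocol article*

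**What the plan says.** Statistical methods for primary and secondary outcomes {20a} writes the PedsQL trajectory model, model (3), in full. It has discrete time, an arm main effect b1, arm-by-visit terms b3j, a normally distributed random intercept, and an independent residual with one variance. The text says the random intercept "captures within-subject correlation, and coefficients for the group-by-time interactions" estimate the arm differences in change. On testing it says: "Individual coefficients can be tested using Wald test, and overall group-by-time interaction can be tested using likelihood ratio test". No random slope, serial correlation, unstructured covariance, robust standard error or baseline constraint is named for PedsQL.

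Four other statements bear on this:

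- The same section justifies mixed models partly by their "flexibility regarding time trend and unequally spaced time points".
- For HBI, model (1) gives each participant random shape parameters with covariance Σ and includes a covariate term. Model (3) has neither.
- Sample size {14} uses a single ICC of 0.5 and four time points, and treats the group-by-time interaction as the test of the main hypothesis.
- Methods for additional analyses {20b} prefers residualized change scores to difference scores in the mediation analysis, because they adjust for baseline and avoid reliability problems.

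**The concern.** Two features of model (3) matter, and they are separate.

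**Free baseline difference.** The arms are randomized, so their expected baseline means are equal. Leaving b1 free estimates a difference known to be zero in expectation. With complete data, b3j then reduces to the arm difference in change from baseline, the kind of score that {20b} avoids for mediation. Precision is lost on a primary outcome.

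**Covariance.** A random intercept with independent, equal-variance errors forces the same variance at every visit and the same correlation 6 weeks apart as 6 months apart. If participants differ in rate of recovery, as model (1) allows for HBI, that structure will not hold exactly. The Wald tests at individual visits would then share one pooled error that is too large for near visits and too small for distant ones. The stated reason for discrete time, too few visits to model a curve, concerns the mean and does not restrict the covariance.

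**Working it through.** **Inputs.** Total size: "We plan to recruit 200 subjects". Allocation: "Randomization will be allocated 1:1 to MSTEP and control", hence 100 per arm. ICC 0.5 and four visits come from Sample size {14}. Visits are taken at 0, 6, about 13 and about 26 weeks. Alpha is named without a value ("The sample size depends on power, type I error rate"), so two-sided 0.05 is assumed. Results are in units of the outcome SD and assume complete data.

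**The plan's own figure.** The protocol states that "our planned sample size of 200 would provide > 99% power to detect a significant group-by-time interaction", conditional on "similar differences in means between the two study groups on HBI and PedsQL as we did in our pilot STEP RCT". The pilot means and SDs are not given, so this can be neither reproduced nor refuted. With the stated size, visits and ICC (noncentral F, 3 and 594 df), 99% power needs a largest arm difference in change of:

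- 0.56 SD if constant after baseline
- 0.59 SD if it peaks at 6 weeks and fades to zero by 6 months
- 0.65 SD if it grows linearly to 6 months

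**Cost of the free baseline difference.** For correlation ρ between baseline and a later visit:

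- b1 free: variance = 2(1 − ρ) × 2/100. At ρ = 0.5 this is 0.020, SE = √0.020 = 0.141 SD.
- Common baseline mean: variance = (1 − ρ²) × 2/100. At ρ = 0.5 this is 0.015, SE = √0.015 = 0.122 SD.
- Ratio = (1 + ρ)/2: 0.75 at ρ = 0.5, 0.65 at ρ = 0.3, 0.85 at ρ = 0.7.

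The constraint therefore removes 25% of the variance (15% to 35% for ρ from 0.7 to 0.3). Put the other way, model (3)'s variance is one third larger (0.020/0.015), and it would need 200/0.75, about 267 participants, to match 200 with the constraint. The difference detectable at one visit with 80% power is 2.80 × 0.141 = 0.396 SD under model (3) and 2.80 × 0.122 = 0.343 SD with the constraint (products from unrounded SEs).

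**Effect of the covariance.** With balanced complete data, model (3) assigns every contrast with baseline a variance proportional to 2(1 − mean ρ), where mean ρ averages all six visit pairs. The true variance is proportional to 2(1 − ρ0j). The Wald error is therefore 2Φ(−1.96 × √[(1 − mean ρ)/(1 − ρ0j)]). Example, exponential decay at 6 months: √(0.500/0.752) is about 0.82, giving 11.0%. The overall test was simulated with 20,000 trials. All decay patterns are assumptions.

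| Pattern | ρ with baseline: 6 wk, 3 mo, 6 mo | Mean ρ | Error 6 wk | Error 3 mo | Error 6 mo | Overall test |
|---|---|---|---|---|---|---|
| Equal | 0.50, 0.50, 0.50 | 0.50 | 5.0% | 5.0% | 5.0% | 5.2% |
| Mild decay | 0.62, 0.55, 0.43 | 0.54 | 3.2% | 4.7% | 7.9% | 5.5% |
| Partial decay | 0.65, 0.49, 0.36 | 0.50 | 1.9% | 5.3% | 8.4% | 5.7% |
| Exponential | 0.73, 0.50, 0.25 | 0.50 | 0.8% | 5.0% | 11.0% | 6.5% |
| Further pattern | 0.60, 0.45, 0.35 | 0.53 | 3.5% | 7.3% | 9.9% | 5.7% |

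The last row is fully simulated, with an overall F test; the closed form gives 3.4%, 7.0% and 9.6%. The other rows use the closed form for the visits and a likelihood ratio test overall. All rows keep the SD equal across visits. If the SD also rises (1, 1.1, 1.2, 1.3, assumed) on top of the exponential pattern, the figures are 0.3%, 4.0%, 10.8% and 6.8%.

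**The case against.** The strongest reply is that the only correlation in the document is a single ICC of 0.5, and under equal correlations model (3)'s standard errors are exact. This stands. A reader might infer that the 6-month PedsQL comparison has an inflated false-positive rate. The document does not support that as fact, because it gives no PedsQL correlations by visit.

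Second, the main hypothesis test is the overall interaction, which moves only mildly, and the per-visit Wald tests are offered as something that can be done. The named comparisons at 6 weeks and 6 months are the first part of the primary analysis, by covariate-adjusted linear regression. A regression at one visit makes no assumption about correlation between visits. This also stands and limits the reach of the covariance point.

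Third, it would be wrong to say that the baseline is wasted. Model (3) uses it as a response, b3j is unbiased, and {20a} lists baseline outcome measures among the potential confounders, so the single-visit regressions may adjust for it. Two limits remain. The general rule in {20a} appears to bring in the baseline outcome only if it is unbalanced, and those regressions do not make the trajectory analysis more precise. Adding time-constant covariates as main effects does not recover the loss in b3j with complete data either.

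Fourth, the missing covariate term in equation (3) can be read as shorthand, since {20a} already requires covariates in all regression analyses. That is fair; it is a matter of tidying the equation.

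None of this answers the efficiency loss, which follows at the protocol's own ICC without any assumed decay. Nor can the model be treated as a detail left to the analysis plan, because the protocol writes it out.

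**Conclusion.** The point holds as a weakness in a stated primary analysis, not as a demonstrated error.

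The firm part is efficiency. At ICC 0.5, 100 per arm and complete data, the free b1 raises the variance of each b3j by one third over a common baseline mean. This concerns precision; validity is not in question.

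The conditional part is the standard errors. If correlation falls with time between visits, the equal-variance patterns examined put the Wald error at about 1% to 3.5% at 6 weeks and 8% to 11% at 6 months, with the overall interaction test at about 5.5% to 6.5%. If correlations are equal, all are about 5%. These ranges rest on assumed correlations and a two-sided 0.05 level. The single-visit regressions are unaffected. The change should be made because it is cheap and remains valid whichever pattern is true.

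**What to change.** First reconcile the number of PedsQL visits. Outcomes {12} and the text introducing model (3) give four, whereas Table 1 marks PedsQL at every weekly assessment as well. Model (3) and the size of its covariance matrix both depend on this.

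Then, in {20a}, restate model (3) as follows:

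- Replace the random-intercept-only structure with an unstructured covariance across the PedsQL visits.
- Keep time categorical, with arm-by-visit terms at each post-baseline visit.
- Constrain the baseline means to be equal across arms by dropping b1. Alternatively, use baseline PedsQL as a covariate with only post-baseline visits as the response.
- Write in the covariates that {20a} already requires.

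The cost is a change of wording before analysis, with no extra data or participants. Four visits need 10 covariance parameters (4 variances and 6 covariances), a small number with 200 participants. If PedsQL is in fact collected weekly, the count rises and the choice of structure should be looked at again.
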